## Abstract

**Background:**

Poorly controlled hypertension (HTN) remains one of the most significant public health problems in the United States, in terms of morbidity, mortality, and economic burden. Despite compelling evidence supporting the beneficial effects of therapeutic lifestyle changes (TLC) for blood pressure (BP) reduction, the effectiveness of these approaches in primary care practices remains untested, especially among African Americans, who share a disproportionately greater burden of HTN-related outcomes.

**Methods/Design:**

This randomized controlled trial tests the effectiveness of a practice-based comprehensive therapeutic lifestyle intervention, delivered through group-based counseling and motivational interviewing (MINT-TLC) versus Usual Care (UC) in 200 low-income, African Americans with uncontrolled hypertension. MINT-TLC is designed to help patients make appropriate lifestyle changes and develop skills to maintain these changes long-term. Patients in the MINT-TLC group attend 10 weekly group classes focused on healthy lifestyle changes (intensive phase); followed by 3 monthly individual motivational interviewing (MINT) sessions (maintenance phase). The intervention is delivered by trained research personnel with appropriate treatment fidelity procedures. Patients in the UC condition receive a single individual counseling session on healthy lifestyle changes and print versions of the intervention materials. The primary outcome is within-patient change in both systolic and diastolic BP from baseline to 6 months. In addition to BP control at 6 months, other secondary outcomes include changes in the following lifestyle behaviors from baseline to 6 months: a) physical activity, b) weight loss, c) number of daily servings of fruits and vegetables and d) 24-hour urinary sodium excretion.

**Discussion:**

This vanguard trial will provide information on how to refine MINT-TLC and integrate it into a standard treatment protocol for hypertensive African Americans as a result of the data obtained; thus maximizing the likelihood of its translation into clinical practice.

**Trial Registration:**

Clinicaltrials.gov NCT01070056

## Background

The disproportionately high prevalence of hypertension (HTN) and cardiovascular disease mortality in African Americans is well documented [1]. The age-adjusted prevalence estimate of HTN in African Americans is 31.8%, compared to 23.3% for whites [2], making African Americans the most highly afflicted group in the United States [3]. Hypertension is the single most common explanation for mortality disparities between African Americans and whites [4]. Fortunately, there is evidence that increased blood pressure (BP) control produces cardiovascular benefits in both African Americans and other ethnic groups [5].

Barriers that hinder adequate BP control exist at the individual level, especially in minority populations [6-8]. Potentially reversible individual-level factors include adverse lifestyle behaviors such as lack of physical activity, high sodium intake, poor intake of fruits and vegetables, and obesity. Several studies have confirmed the negative association between adverse lifestyle behaviors and blood pressure [9-14]. The *efficacy *of lifestyle interventions in the prevention and treatment of HTN is well proven [12-20]. Well-studied lifestyle approaches include weight loss;[21-23] restriction of sodium intake;[9,15,17,20,24,25] a diet rich in low-fat dairy and, fruits and vegetables;[18,25,26] limited alcohol intake;[27,28] and regular exercise [23,29-31]. For example, SBP/DBP reductions of 5.5/3.0 mm hg (comparable to those observed in drug trials) were achieved in the Dietary Approaches to Stop Hypertension (DASH) study, where patients were randomized to receive a diet rich in fruits and vegetables and higher in low-fat dairy products versus a standard diet [18]. The BP reduction was particularly high in African Americans in the DASH trial. A later lifestyle trial, PREMIER, showed that lifestyle changes were more effective in BP reduction than advice only [16]. Further analysis of PREMIER data indicated that BP reductions were similar or higher among African-American patients compared to whites;[32] and these intervention effects were maintained 18 months post-intervention [19]. Other trials such as the Trials of Mild Hypertension Study, Hypertension Control Program, Trial Of Nonpharmacologic interventions in the Elderly (TONE), Trials of Hypertension Prevention-Phase II, Diet, Exercise and Weight Loss Intervention Trial and the Primary Prevention of Hypertension have all reported similar beneficial effects of lifestyle changes on BP reduction [12,13,15,17,19,33-36]. Based on this evidence, non-pharmacologic approaches to BP control have been adopted as standard treatment in hypertensive patients by the Joint National Committee on Detection, Evaluation and Treatment of Hypertension (JNC)-5, JNC-6, and JNC-7 treatment guidelines [5,37,38]. However, all of these studies were conducted in clinical settings, under controlled conditions. If these interventions cannot find a place in clinical practice settings, their impact on public health will be negligible. This is particularly true for African Americans, given their poorer BP control compared to other racial/ethnic groups,[39] as well as their low participation rates in these trials. The current study represents an advance in the non-pharmacologic treatment of HTN in high risk populations because it emphasizes the translation of an empirically-validated TLC intervention into clinical practice.

### Study Aims

The primary aim of the Therapeutic Lifestyle Changes in Clinic (TLC-Clinic) trial is to test the effectiveness of a practice-based comprehensive therapeutic lifestyle intervention, delivered through group-based counseling and motivational interviewing (MINT-TLC) versus a Usual Care control condition (UC) in reducing BP, among 200 low-income, poorly controlled hypertensive African-American patients. The secondary aims are to evaluate the effect of MINT-TLC versus UC, on changes in the following lifestyle behaviors from baseline to 6 months: a) physical activity, b) weight loss, c) number of daily servings of fruits and vegetables and d) 24-hour urinary sodium excretion. In addition, a secondary aim will evaluate the effect of MINT-TLC versus UC on BP control at 6 months.

We hypothesize that patients randomized to the intervention condition (MINT-TLC) compared to those randomized to the UC condition, will exhibit a greater reduction in systolic BP (SBP) and diastolic BP (DBP) at 6 months; greater levels of physical activity; greater percent change in weight; increased intake of fruits and vegetables; reduced 24-hour urinary sodium excretion; and a higher proportion of patients will have adequate BP control at 6 months. This study is one of few trials to test the effectiveness of this approach among minority populations who receive care in primary care practices.

## Methods/Design

### Study Design

TLC-Clinic is a randomized controlled trial (RCT) with two conditions: Intervention condition (MINT-TLC) and Usual Care condition (UC). Approximately 200 African-American patients with uncontrolled HTN will be randomly assigned to either the MINT-TLC or UC conditions. The MINT-TLC intervention is based on established clinical practice guidelines for prevention and treatment of HTN, which recommends weight loss (if overweight), limiting sodium and alcohol intake, regular physical activity, and eating a low-fat diet that is rich in fruit and vegetables. MINT-TLC will be conducted by trained Health Educators. Patients attend 10 weekly group classes (intensive phase) followed by individual monthly motivational interviewing (MINT) sessions for 3 months (maintenance phase). Makeup sessions are built in after sessions 4 and 9 for group members who missed any of the previous sessions. Assessments are conducted at baseline (visit 1), 3 months (visit 2), and 6 months (visit 3). Participants receive $20 at the completion of baseline assessment, $10 at the 3-month visit, and $20 at the completion 6-month visit ($50 total) for their time and effort in the study. All participants also receive free metro cards to help facilitate transportation to and from the study site for the individual counseling visit (UC condition) or group classes (MINT-TLC). The primary and selected secondary outcomes are assessed at the 3 month visit, and all outcomes are assessed at the 6-month follow-up visit.

### Study Sites and Population

This study is being conducted within the Ambulatory Care Practice of the Bellevue Hospital Center (BHC), the largest comprehensive diagnostic center within the New York City Health and Hospitals Corporation. Approximately 20,000 patients receive treatment annually at BHC's adult medicine primary care practice, with just under 60,000 visits in 2009. To be eligible, patients must self-identify as black/African American, be at least 18 years old, currently receive care within the Ambulatory Care Practice and have had at least two appointments in the past year, have a diagnosis of HTN with uncontrolled BP on at least two visits in the past year (SBP ≥ 140 mmHg *or *DBP ≥ 90 mmHg or SBP ≥ 130 mmHg *or *DBP ≥ 80 mmHg for patients with diabetes or chronic kidney disease). In addition, all patients must have uncontrolled BP at the time of the consent visit, as measured by WatchBP (Microlife; Golden, CO), an oscilliometric validated BP monitor [40,41]. Patients are excluded if they are non-English speaking, participate in other HTN trials, have an arm circumference > 42 cm, have cognitive impairment based on the Comprehensive Assessment and Referral Evaluation Dementia Diagnostic Scale (CARE-DIAG) score ≥ 6 for patients age 60 and older,[42,43] are unwilling/unable to comply with the study protocol (either self-selected or by indicating that they could not complete all requested tasks including attending intervention classes if they were to be randomized to the MINT-TLC group), or unwilling/unable to provide informed consent. All patients who agree to take part in the study are asked to provide informed consent. The study was approved by the Institutional Review Boards of New York University and Bellevue Hospital Center. The study is monitored by a Data Safety Monitoring Board.

#### Recruitment

Three main approaches are used to recruit patients into this study. First, potentially eligible patients are identified through a review of electronic medical records (EMR) using the ICD-9 billing codes for HTN (401-401.9). The physicians of eligible patients are notified of their patients' potential eligibility, and then asked permission to enroll their patients in this study. After consent is obtained from the physicians, eligible patients are approached by research assistant's (RA) at their next clinic appointments for screening, consent and baseline visit. Second, physicians are asked to identify hypertensive patients in their practices through the use of ICD-9 billing codes. Once a patient is identified who fulfills the inclusion criteria, the RA calls the patient and invites him or her to complete the eligibility screen, and if eligible, to consent and complete the baseline visit. Study investigators ([name]) also conduct in-service visits at the study sites prior to patient enrollment and every 3 months thereafter to explain the study rationale, its significance and procedures. At this time, physicians are given a business card that lists eligibility criteria and contact information for the RAs. Finally, flyers are hung in the waiting room of the Ambulatory Care Practice and RAs approach patients about the study in the waiting areas.

#### Randomization

After completion of consent procedures and baseline data collection, a list of patient identification numbers is sent on a weekly basis to the data management team to be randomized in a 1:1 ratio to either the MINT-TLC or UC group. This project has a hierarchical study design with each patient nested within a primary care physician and patients are recruited at different times. Randomization is within primary care physician. Therefore, a randomization algorithm developed by the Data Coordinating Center at the Research Division of the Hebrew Home at Riverdale was used; this algorithm has yielded balanced groups for numerous studies. This randomization procedure is carried out using a SAS macro after a subject completes the baseline interview. A random number from 0 to 1 is used to determine the assignment group. The standard cut score is set at 0.5 for the first n subjects from the same provider, 4 for this study. Those who receive a random number between 0 and 0.5 are assigned to the control group and those with a random number greater than 0.5 are assigned to the intervention group. The balance between the groups within each provider is weighted carefully after the total number of subjects from a group reaches a pre-specified number. If more than the n subjects are randomized initially, the cut score for the next subject is equal to the ratio of the experimental group (n1) to the subjects already randomized (m) for that group (n1/m). The cut score is adjusted according to the previous number of subjects randomized.

Patients are informed of the results of randomization by an RA in person or by phone; at this time, the RA discusses the intervention/counseling session schedule, and answers any additional questions. Given the nature of the intervention, it is impossible to blind the RAs to the assigned condition. However, the dimension that the RA's knowledge of the assigned condition could possibly affect is the BP measurement - the primary outcome of this study. To reduce the potential for this bias, we use an automated BP device (WatchBP). Neither the RA nor the patients see the measurements during this process, which prevents the RA from influencing the BP readings.

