Based on our own clinical experience and estimates from other clinical trials in uncontrolled hypertensive patients,[16-18,20,53-57] we estimate that the cross-sectional standard deviations (SD) of SBP and DBP at baseline will be about 15/12 mm Hg. It was assumed that the SD at follow-up will be as much as 25% larger in the MINT-TLC group, and that the correlation between baseline and follow-up BPs will be 0.6 in the UC group and 0.4 in the MINT-TLC group (possibly as a result of heterogeneity of treatment response). Design effects of patients clustered within physicians has been found to be minimal in our experience; for example the intracluster correlation coefficient (ICC) was estimated to be 0.02 or less, and cluster sizes are relatively small. Clustering results in reduction in power and increased requirements for sample size. The variance inflation factor (VIF) used in power calculations involving clustering depends on the size of the cluster (number of patients treated by each physician) and ICC. Power calculations were examined in sensitivity analyses (not shown), assuming that heterogeneous variances may require modeling. The original power calculations were updated using actual data from the beginning of the trial. It was found that the average cluster size was 1.55 (SD = 1.39, ranging from 1 to 10 clusters and the total number of physicians was 92). The following assumptions were used in the power calculations: σ (population standard deviation) = 15 for SBP and 12 for DBP; α = 0.05, two-tailed; R = 0.9 (reliability); g = 2 (groups); n = 3 (waves, t = 0, 3 and 6 month); $s_{x}^{2}$(variance of time) = 0.125; inflation factor (IF) = 1+(clustersize-1)*ICC with clustersize = 1.55 and ICC = 0.01.

Thus, 100 subjects per group will provide 80% power to detect a 6 to 7 mm Hg differential change in SBP and a 5 to 6 mm Hg differential change in DBP, based on testing the Time (pre through post-intervention waves) × Group interaction in a mixed model, allowing for heterogeneous variances, serial correlations and modeling of design effects. As described below, analyses will be performed under an intent-to-treat design; therefore all patients, including those who drop out of the study will be invited back for the final assessments.

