### Analysis of the Primary Aim

The primary pre-planned analyses are to examine SBP and DBP separately; however, if the two variables are correlated, MANOVA will be used to test the hypothesis that those assigned to MINT-TLC will, on average, exhibit greater 6-month decreases in SBP and DBP than those assigned to the UC condition. A mixed (fixed and random) effects model using SAS Proc Mixed is the method planned for use. Such models permit modeling heterogeneous group variances and serial correlations over time as well as the design effects of clustering. Moreover, the use of the missing data algorithms within the mixed procedure permits the inclusion of all individuals with at least one wave of data. The primary test concerns the Group × Time interaction, and the resulting F-test will provide the primary "intent-to-treat" test of the hypothesis. If this is statistically significant at the two-tailed α = 0.05 level, the magnitude of the treatment effect will be estimated with 95% Confidence Interval (CI), separately for SBP and DBP. The expectation is that the randomization of patients to treatment arm and the absence of significant selection and/or attrition biases will obviate the need for any covariates in the analysis. This has been the normative experience of the data coordinating center in over 100 randomized trials. However, in the unlikely event that imbalances are identified, propensity score analyses or other methods will be used to condition on the covariates. The predicted values of those analyses will be included as covariates together with the group by covariate interactions in the model. This procedure is most often applied in quasi-experimental and observational studies.

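### Within-physician balancing is largely nominal, though nearly harmless; separately, the imbalance-triggered covariate rule should give way to pre-specified baseline adjustment

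*Protocol article*

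**What the plan says.** **Allocation (protocol article, Randomization).** Patients are "to be randomized in a 1:1 ratio to either the MINT-TLC or UC group". The section states: "Randomization is within primary care physician". It supports the choice of method by its record: "this algorithm has yielded balanced groups for numerous studies". The rule itself is: "The standard cut score is set at 0.5 for the first n subjects from the same provider, 4 for this study". Only beyond that point does the cut score become the share of that provider's patients already in the experimental arm, which pulls the next assignment back towards balance.

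**Cluster sizes (Sample Size and Power Analysis).** From data early in the trial, "the average cluster size was 1.55 (SD = 1.39, ranging from 1 to 10 clusters and the total number of physicians was 92". I read the range as 1 to 10 patients per physician. The power calculation uses an intracluster correlation (ICC) of 0.01, and the text puts it at 0.02 or less.

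**Primary analysis (Analysis of the Primary Aim).** The test is the Group × Time interaction in a mixed model. The authors expect that randomization, together with no important bias from selection or dropout, "will obviate the need for any covariates in the analysis". If imbalances are nevertheless found, propensity scores or other methods are brought in, with the predicted values and group-by-covariate interactions added to the model.

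**Comorbidity (Chart Extraction Data).** The Charlson index will be used to adjust for the effect of comorbidity on BP.

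**The concern.** There are two distinct points.

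First, the description of allocation promises more than the rule delivers. If most physicians contribute one or two patients and the correction starts at the fifth, the scheme is close to simple randomization. Nothing in it constrains baseline BP or diabetes/CKD status either.

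Second, and independently of the allocation rule, the covariate plan is conditional. The primary model is unadjusted unless an inspection of the data shows imbalance, and then it changes form. The primary estimate and p-value then depend on a choice made after seeing the data. The default also forgoes the precision available from baseline BP, which is measured on everyone. The Charlson statement sits awkwardly with both halves of that rule, since it promises an adjustment that the primary-aim section expects not to need.

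**Working it through.** **1. Share of allocations made by coin toss.** Inputs: 92 physicians, mean 1.55, SD 1.39, sizes 1 to 10, threshold 4. The total is 143, because 143/92 = 1.554 rounds to 1.55 while 142/92 = 1.543 does not. Integer cluster-size distributions that match these figures, with at least one physician of size 10, were enumerated. For each, the patients beyond a provider's fourth were counted. The extremes are:

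- Most beyond the fourth: sizes 10, 8, 6, 6, then 25 physicians with two and 63 with one (SD 1.394). Beyond the fourth: 6 + 4 + 2 + 2 = 14. Coin tosses: 129/143 = 90.2%.
- Fewest beyond the fourth: sizes 10, thirteen of 4, one of 3, one of 2, and 76 of 1 (SD 1.386). Beyond the fourth: 6. Coin tosses: 137/143 = 95.8%.

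Simulating the documented rule on these two distributions gives an expected sum of within-physician arm differences of 93 and 100. Pure coin tossing gives 96 and 101, so the rule reduces imbalance by about 3% and 1%.

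**2. What the lost physician balance costs.** At ICC 0.01 to 0.02, even perfect within-physician balance would remove about 1–2% of variance. Before the clustering factor, the SBP detectable difference is 6.46 mm Hg. It would become 6.46 × √0.99 = 6.43 or 6.46 × √0.98 = 6.40.

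**3. The plan's detectable difference.** Inputs: SD 15 (SBP) and 12 (DBP); follow-up SD 25% larger in MINT-TLC; baseline-to-follow-up correlation 0.6 (UC) and 0.4 (MINT-TLC); 100 per arm; 80% power; two-sided 0.05; inflation factor 1 + 0.55 × 0.01 = 1.0055.

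Formula: difference = (1.960 + 0.842) × √[(V_UC + V_MINT) × 1.0055 / 100].

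Variance of change, SBP:
- UC: 2 × 225 × (1 − 0.6) = 180
- MINT-TLC: 225 + 351.6 − 2 × 0.4 × 15 × 18.75 = 351.6
- Sum 531.6, giving **6.48 mm Hg** (stated: 6 to 7)

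DBP: 115.2 + 225 = 340.2, giving **5.18 mm Hg** (stated: 5 to 6).

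Both fall inside the plan's ranges. A slope formula using the stated reliability 0.9 and time variance 0.125 gives 3.07 or 5.32 mm Hg for SBP, depending on how the time variance is entered, and does not reproduce them. The match therefore rests on the SDs and correlations.

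**4. The same design adjusted for baseline.** Residual variance = follow-up variance × (1 − r²).

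- SBP: 225 × (1 − 0.36) + 351.6 × (1 − 0.16) = 144 + 295.3 = 439.3. Ratio 439.3/531.6 = 0.83, a 17% reduction. Detectable difference **5.9 mm Hg**.
- DBP: 144 × 0.64 + 225 × 0.84 = 92.2 + 189 = 281.2. Detectable difference **4.7 mm Hg**.

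This gain would be almost unchanged if every physician's patients were perfectly balanced.

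**The case against.** Much of the case on the other side stands.

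- *Within-physician balance is not what justifies the unadjusted analysis.* A reader might infer this from the two sections together. The primary-aim section instead names randomization and the absence of selection or attrition bias, plus the coordinating centre's experience across its trials. Coin-toss allocation satisfies the randomization part in full.
- *Arm sizes are not at risk.* A reader might infer that near-simple randomization threatens the 1:1 ratio. Trial Status reports 83 of 166 patients in MINT-TLC. With 34 to go, pure coin tosses would give 100 ± 1.96 × √(34 × 0.25), about 94 to 106 per arm. Equal totals do not show balance on covariates or within physicians, but the concern about totals is gone.
- *The 90% figure belongs to the early data.* If the number of physicians stayed at 92 (an assumption), the mean would be 166/92 = 1.80 now and 200/92 = 2.17 at the end. The documents do not settle the share at 200.
- *No within-physician scheme could do much here.* In the two extreme distributions, 63 to 76 of the 92 physicians have a single patient. Some run-in is also needed, since applying the ratio rule from the second patient would make that assignment deterministic. With 166 of 200 enrolled and the cost of lost balance so small, changing the allocation scheme is not warranted.
- *The plan is not underpowered or biased as it stands.* Chance baseline differences are already counted in the variance behind the 6 to 7 mm Hg figure. Baseline adjustment improves efficiency; it does not repair an invalid test.

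It can also be said that covariate lists usually belong in an analysis plan that is not shown. That excuses a missing list. It does not cover a rule the article does state, under which the form of the primary model depends on what the data show.

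**Conclusion.** A minor point with two parts.

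The within-physician balancing is largely nominal: 90–96% of allocations in the 143-patient snapshot were made at a cut score of 0.5. Validity is untouched, and the cost is about 1–2% of variance if the ICC is 0.02 or less. Only the description needs correcting.

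The more useful part is the analysis. The imbalance trigger makes the primary model data-dependent, and the unadjusted default gives up about 17% of variance (SBP detectable difference about 6.5 to 5.9 mm Hg, DBP 5.2 to 4.7). These figures assume the plan's SDs and correlations, complete data on 100 per arm, and a comparison of baseline with 6 months that ignores the 3-month wave. The further gain from diabetes/CKD status cannot be sized from the document.

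**What to change.** 1. **Randomization.** State that allocation is effectively simple 1:1 randomization, with a within-provider correction from the fifth patient that applied to few patients. Drop the implication of within-physician balance. Leave the scheme unchanged.
2. **Analysis of the Primary Aim.** Delete the imbalance-triggered propensity step and its interactions from the primary model. Pre-specify adjustment for baseline BP in one of two forms: baseline as a covariate with the 3- and 6-month values as outcomes, or all three waves as outcomes with baseline means constrained equal across arms. The second form keeps patients who have only a baseline value, in line with the plan's intention to include everyone with at least one wave. Name the 6-month group contrast as the primary test.
3. **Diabetes/CKD status.** Add it as a pre-specified covariate, since it already sets the BP threshold for eligibility and control.
4. **Chart Extraction Data.** Reconcile the Charlson statement with this model. Either list the baseline Charlson score among the covariates or assign that adjustment to a sensitivity analysis.

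The cost is wording only, agreed before outcome data are examined. Baseline BP is already collected, and diabetes/CKD status is already needed to apply the eligibility and control thresholds.
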